#### Sample size

We plan to recruit a total of 720 participants (120 at each site), allowing for a predicted 15% drop out at 6 months post-birth, resulting in 612 participants for analyses.

A similar intervention, the RUBY Study (Forster et al., 2017) was able to follow-up 88% of participants so we believe a 15% drop-out rate is likely conservative.

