#### Analysis

Data from telephone/email surveys at baseline prior to birth, 6 weeks, 4 months and 6 months will be entered into a matrix in REDCap ©, an electronic data collection program by the research team. This data will be collated into Excel, cleaned and analysed, with supervision by the biostatistician. Data will be coded, Statistician and Health Economist will remain blinded throughout the length of the study.

Peer worker interactions with participants will be logged, along with notes about factors which might affect uptake (i.e. participants not available to respond, other priorities such as funerals) so as to undertake process analysis, in addition to outcome analysis. This will be scanned/emailed to the research team for analysis.Interactions with participants will be logged by peer workers (on paper/electronic, stored in a locked secure environment at the site, then emailed or scanned to the research team and entered into REDCap©) to ensure scheduled visits had occurred, and to record any issues that could be incorporated into a process analysis (e.g. participant did not respond, participant had moved).We will use ‘journal’ reflective practice data for analysis of Aboriginal peer workers’ interactions [24].

We plan to recruit at least 360 participants and 306 participants completing 6 weeks in both of group 1 (intervention) and group 2 (control), with three sites in each group (120 participants and 102 completing 6 weeks per site assuming 15% drop out) providing 80.1% power to detect a difference between the group proportions of 0.1500. The proportion in group 1 (the treatment group) is assumed to be 0.2500 under the null hypothesis and 0.4000 under the alternative hypothesis. The proportion in group 2 (the control group) is 0.2500. The test statistic used is the two-sided Z-Test (Pooled), the intra-cluster correlation is 0.0100 and the significance level of the test is 0.050.

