At 6 weeks we expect a prevalence of exclusive breastfeeding to be 25% in the control group, based on breastfeeding prevalence of 26% seen at 6 weeks in the Gudaga study (Craig et al., 2011) while if effective we estimate prevalence of exclusive breastfeeding in the intervention group to be 40% or more. A Cochrane review by McFadden et al. [18] reported women in intervention groups were less likely to stop exclusive breastfeeding by 6 weeks (RR 0.79, 95% CI 0.71 to 0.89)., which applied to a base rate of 75% stopping breastfeeding leads to 15% higher absolute breastfeeding rates at 6 weeks (40% vs. 25%). However, we consider the current study intervention to be more intense than other studies included in that meta-analysis.

Elliot-Rudder [19] conducted a cluster RCT where health professionals were trained in motivational interviewing to support women to continue breastfeeding. In a sample of 330 women, with the outcome of exclusive breastfeeding at 4 months (OR 1.88, 95% CI 1.01–3.6, p = 0.047), this study was able to demonstrate effectiveness of the intervention.

We plan to use survival analysis to assess one of our secondary outcomes (using another outcome, days of exclusive breastfeeding).

We will recruit approximately 120 mother – babies in each of six sites (aiming for 40 per year for 3 years, given approximately 80–100 births per year in each site).

Primary outcomes: (a) Exclusive breastfeeding at 6 weeks (24 h recall telephone questionnaire or via survey email). (b) Exclusive breastfeeding at 4 months (24 h recall telephone or survey email) (c) Exclusive breastfeeding at 6 months (24 h recall telephone or survey email).

Secondary outcomes: (a) Initiation of breastfeeding within first 24 h (self – report, 6 week survey), (b) Days of exclusive breastfeeding (self-report) (c) Days of any breastfeeding (self-report) (d) Age at introduction of expressed breastmilk (self-report). (e) Age introduction of solid/semi-solid food (self-report) (f) Age at introduction of other breastmilk substitutes (self-report) (g) Reason for cessation of breastfeeding including contraindications to breastfeeding (self-report) (h) Hospitalisation in first 6 months of life (self – report at six months) (i) Otitis media requiring antibiotics in first six months of life (self – report at six months). (j) Breastfeeding at 12 months (SMS – yes/ no).

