#### Trial governance

The project will appoint an Aboriginal Steering Committee, including investigators, midwife/ves, AHWs and consumers who will meet biannually. The purpose of the steering committee will be to advise the research team about appropriate service delivery models.

A subgroup of investigators will form the Data Monitoring Committee which will meet annually to review data security and quality and accuracy of data collection.

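### Infant hospitalisation and otitis media rest on a single report at six months, so a family missed at that survey contributes nothing even if it answered at 6 weeks and 4 months

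*Protocol article*

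**What the plan says.** The secondary outcomes are listed in the Analysis section under RCT. Item (h) is "Hospitalisation in first 6 months of life (self – report at six months" and item (i) is "Otitis media requiring antibiotics in first six months of life (self – report at six months". Both cover the whole of the first six months, and both are tied to the six-month report.

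The same mothers are contacted earlier. The Data collection section lists postnatal surveys at 6 weeks, 4 months and 6 months, and the Analysis section confirms it: "Data from telephone/email surveys at baseline prior to birth, 6 weeks, 4 months and 6 months will be entered into a matrix in REDCap". The only later contact is a text message with one item, "Breastfeeding at 12 months (SMS – yes/ no", which carries no health events. The article describes no record linkage, chart review or other systematic source for (h) and (i).

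On loss to follow-up, the Sample size section plans for 720 participants, "allowing for a predicted 15% drop out at 6 months post-birth, resulting in 612 participants for analyses". The power statement in the Analysis section attaches the same 15% to an earlier time: "120 participants and 102 completing 6 weeks per site assuming 15% drop out".

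**The concern.** Items (h) and (i) are the only infant-illness events among the listed outcomes, and the Background motivates the trial partly by such illness. With one report at the end, a family that answered at 6 weeks and 4 months and then drops out has no value for either outcome, even if the admission was in the first month. Families who stay must recall six months at once, although they were asked other questions twice in between.

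Two things are at stake. The first is missing data that could partly be avoided at contacts already planned. The second is possible bias. The analysis would be confined to families reached at six months, and only intervention families have a peer worker in regular contact, so retention could differ by arm. If loss also depends on whether the infant was ill, the comparison of event proportions would be distorted.

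**Working it through.** **Inputs from the article.** 720 recruited, 15% lost and 612 analysed (Sample size); 306 per arm, 102 per site and ICC 0.01 (Analysis); surveys at 6 weeks, 4 months and 6 months (Data collection).

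**The plan's own figure.** 720 × (1 − 0.15) = 612, which reproduces.

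**Families with no value for (h) or (i).** 720 − 612 = 108, that is 54 per arm or 18 per site.

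**Infant-months covered with one report at six months.** 612 × 6 = 3672 of 720 × 6 = 4320, which is 85.0%.

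**Infant-months covered if both items are also asked at 6 weeks and 4 months.** The result depends on when the 108 families were last reached. The limiting cases, with 6 weeks = 42/30.4375 = 1.38 months, are:

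| All 108 last reached | Infant-months added | Covered | Share of 4320 | Families with partial data |
|---|---|---|---|---|
| before the 6-week survey | 0 | 3672 | 85.0% | 0 |
| at 6 weeks | 108 × 1.38 = 149 | 3821 | 88.4% | 108 |
| at 4 months | 108 × 4 = 432 | 4104 | 95.0% | 108 |

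**Where the plan sits in that range.** The article does not settle it. The Sample size section reaches 612 at six months and the power statement reaches 6 × 102 = 612 at six weeks. Read literally together, nobody is lost between those surveys and no lost family is recovered. If instead 15% are gone by six weeks and more leave later, the six-month loss exceeds 15%: an assumed 20% would be 144 families and 25% would be 180. At 12% loss, the complement of the 88% follow-up cited from a similar study, it would be about 86.

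**When the single report causes bias.** Let p be the true event proportion, and let r₁ and r₀ be the retention of families with and without an event. The observed proportion is p·r₁ / [p·r₁ + (1 − p)·r₀].

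- If r₁ = r₀, this equals p. Unequal retention between arms alone does not bias the proportion.
- Illustration with assumed values: p = 20% in both arms, and families with an event twice as likely to be lost. At 10% total loss the two loss rates are 16.7% and 8.3%, and the observed proportion is 0.20 × 0.833/0.90 = 18.5%. At 20% total loss they are 33.3% and 16.7%, and it is 0.20 × 0.667/0.80 = 16.7%. Arms with these two loss rates would differ by about 1.9 points with no true effect.
- For scale: the design effect is 1 + 101 × 0.01 = 2.01 and the effective size is 306/2.01 = 152 per arm. The 95% half-width for a difference at 20% is 1.96 × √(2 × 0.20 × 0.80/152) ≈ 9 points.

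None of the event rate, the loss by arm or the link between loss and illness is in the article. The illustration shows the mechanism, not an estimate.

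**The case against.** An outcome over six months that is reported at six months is internally consistent, and nothing in the text contradicts it. Both outcomes are secondary. The gain from asking earlier may be nil, since the article's two statements of the 15% loss can be read to mean that nobody leaves between 6 weeks and 6 months. Any plausible bias may also be small beside the imprecision of the comparison. All of this stands, and it keeps the severity low. It does not remove the point: the gain can also be as much as 10 percentage points of coverage, and shorter recall helps every family whenever losses occur.

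The schedule figure and questionnaires were not available, so an earlier health item cannot be fully excluded. That stands too, although the text fixes the report at six months for exactly these two outcomes, and assigns a different survey (6 weeks) to initiation of breastfeeding.

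A reader might also infer that no illness can come to the team's notice before six months. The article does not support that. Research staff contact mothers at 6 weeks and 4 months, peer-worker logs are sent to the research team, and reasons for stopping breastfeeding are collected. None of these captures events systematically, and the logs cover only the intervention arm. Nor is this a finding about safety oversight: the committee's stated remit ("will meet annually to review data security and quality and accuracy of data collection") is a separate matter from when two outcomes are asked.

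**Conclusion.** The point holds as a low-severity weakness in how two secondary outcomes are collected. At the planned 15% loss, 108 of 720 families give no information on hospitalisation or otitis media, whatever they answered earlier. Using the two existing earlier surveys would raise infant-month coverage from 85.0% to somewhere between 85.0% and 95.0%. This rests on the 15% applying at six months and on no earlier health item existing. The primary outcomes, which use 24-hour recall at each survey, are unaffected.

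Two stronger readings are tempting and not supported. One is that better retention in the intervention arm would raise its recorded event rate and mask a benefit. That requires loss to depend on illness, with families of ill infants the more likely to leave; if they were the more likely to stay, the direction would reverse. The other is a definite share recovered. Spreading the losses evenly over the three intervals would give partial data on 72 of the 108 families, but the article gives no such pattern, and its two placements of the 15% point to little or no later loss.

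**What to change.** Ask hospitalisation and antibiotic-treated otitis media at 6 weeks, 4 months and 6 months, each covering the time since birth or since the last survey the mother answered, so that a skipped survey leaves no gap. Change the wording of (h) and (i) so that they are derived from the accumulated reports.

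The derivation must account for time observed. A family last reached at 4 months without an event is event-free to 4 months, not to six. Counting early events from lost families while discarding the event-free ones would inflate the proportion. A time-to-first-event analysis or a rate per infant-month avoids this.

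In the same revision, state whether the 15% loss applies at 6 weeks or at 6 months, since the likely gain depends on it.

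The cost is two short items added to two existing surveys and a change to the REDCap forms. No new contact is needed. The downside is a slightly longer survey at those two contacts.

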**Methods:**

We will evaluate the effect of scheduled breastfeeding peer support for and by Aboriginal women, on breastfeeding initiation and the prevalence of exclusive breastfeeding. This MRFF (Medical Research Future Fund) funded project is designed as a single-blinded cluster randomised controlled trial recruiting six sites across New South Wales, Australia, with three sites being randomised to employ a peer support worker or undertaking standard care. Forty pregnant women will be recruited each year from each of the six sites and will be surveyed during pregnancy, at six weeks, four and six months postnatally with a single text message at 12 months to ascertain breastfeeding rates. In-depth interviews via an Indigenous style of conversation and storytelling called ‘Yarning’ will be completed at pre- and post-intervention with five randomly recruited community members and five health professionals at each site” [5]. Yarns will be audio recorded, transcribed, coded and thematic analysis undertaken. Health economic analysis will be completed to assess the health system incremental cost and effects of the breastfeeding intervention relative to usual care.

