#### Data collection

A research assistant or associate research fellow will collect data. The research team will call potential participants that have provided their contact details. They will again be verbally given information about the project, from the PIS and will be asked to provide verbal consent. Surveys will be collected at these time-points (see Fig. 2):

Baseline (32–40 weeks of gestation).6 weeks post-birth (after which a $50 voucher will be sent to participant).4 months post-birth.6 months post-birth.12 months post-birth (SMS message).

If participants are not contactable by telephone after three attempts, a link to the survey will be emailed to them or sent via SMS (to a maximum of three times over three weeks). Permission will also be requested for the maternal and child health team to inform peer workers when the women have given birth to their babies, in order to ensure early access to the intervention.

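### Breastfeeding at 12 months rests on one yes/no text with no stated reminder and no stopping age, so outcome (j) is at risk of non-response bias and outcome (c) is only coarsely censored after six months (minor)

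*Protocol article*

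**What the plan says.** Three places in the protocol article describe the 12-month contact, and they agree.

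- The Analysis section lists secondary outcome (j) as "Breastfeeding at 12 months (SMS – yes/ no".
- The Methods part of the abstract says women are surveyed up to six months, "with a single text message at 12 months to ascertain breastfeeding rates".
- The Data collection section ends its list of time points with "12 months post-birth (SMS message".

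The Data collection section also has a repeat-contact rule: "If participants are not contactable by telephone after three attempts, a link to the survey will be emailed to them or sent via SMS". The number of sends is capped at three within a three-week period. Failed telephone calls trigger the rule, and what it sends is a survey link. It is not said to cover the 12-month text.

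On duration, outcome (c) is "Days of any breastfeeding (self-report", with no time limit. Outcomes (h) and (i) in the same list are expressly confined to the first six months of life. Outcome (g) is "Reason for cessation of breastfeeding including contraindications to breastfeeding (self-report". The survival analysis that is named concerns exclusive breastfeeding: "We plan to use survival analysis to assess one of our secondary outcomes (using another outcome, days of exclusive breastfeeding".

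The article gives no expected rate of any breastfeeding at 6 or 12 months and no expected reply rate to the text. Its 15% dropout allowance (Sample size section) is for six months.

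**The concern.** Two things are lost at the point of data capture.

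First, a woman who has stopped may have less reason to answer a text about breastfeeding than one who continues. This is a judgement; the documents do not say it. If it is so, repliers over-represent women still breastfeeding and the 12-month prevalence is too high. Reply patterns could also differ between arms, because only the intervention arm has had months of calls and texts from a peer worker.

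Second, a yes/no answer carries no age at stopping. Outcome (c) is open-ended, yet after the six-month survey nothing further is asked that would give a number of days. The Background cites national guidance to continue breastfeeding to 12 months and beyond, so this period is of interest. A later analysis plan can choose how to handle censoring, but it cannot recover a stopping age that was never asked.

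**Working it through.** **The plan's own figure.** The only power figure is for exclusive breastfeeding at six weeks (Analysis section: 306 per arm, 102 per site, ICC 0.01, 0.25 against 0.40, two-sided pooled Z-test at 0.05).

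- Design effect = 1 + (102 − 1) × 0.01 = 2.01. Effective n per arm = 306 / 2.01 = 152.2.
- Pooled SE = √(2 × 0.325 × 0.675 / 152.2) = 0.0537. SE under the alternative = √((0.25 × 0.75 + 0.40 × 0.60) / 152.2) = 0.0530.
- Power = Φ((0.15 − 1.96 × 0.0537) / 0.0530) = 80.1%.

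This matches the article. It uses nothing from the 12-month contact.

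**Prevalence at 12 months.** Every input below is an assumption, because the article gives none. Let p be the true prevalence, and let a and b be the reply rates of women who are and are not still breastfeeding. Then

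prevalence among repliers = p·a / (p·a + (1 − p)·b).

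Now suppose a share s is still breastfeeding at six months and a share f of those continues to 12 months, so p = s·f. If earlier reports of stopping are counted as no and the text is used only for the rest,

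prevalence = s × f·a / (f·a + (1 − f)·b).

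This also assumes that feeding status at six months is known for all and that the same a and b apply within the group still breastfeeding then.

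| s, f | true p | reply a / b | repliers only | earlier stoppers counted as no |
|---|---|---|---|---|
| 0.20, 0.4 | 8% | 60% / 60% | 8.0% | 8.0% |
| 0.20, 0.4 | 8% | 70% / 50% | 10.9% | 9.7% |
| 0.20, 0.4 | 8% | 80% / 40% | 14.8% | 11.4% |
| 0.30, 0.4 | 12% | 60% / 60% | 12.0% | 12.0% |
| 0.30, 0.4 | 12% | 70% / 50% | 16.0% | 14.5% |
| 0.30, 0.4 | 12% | 80% / 40% | 21.4% | 17.1% |
| 0.45, 0.6 | 27% | 60% / 60% | 27.0% | 27.0% |
| 0.45, 0.6 | 27% | 70% / 50% | 34.1% | 30.5% |
| 0.45, 0.6 | 27% | 80% / 40% | 42.5% | 33.8% |

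Worked case at 12% with 80% / 40%: 0.096 / (0.096 + 0.352) = 21.4%, an excess of 9.4 points. With earlier stoppers counted as no: 0.30 × 0.32 / (0.32 + 0.24) = 17.1%, an excess of 5.1 points. The derivation rule shrinks the bias but does not remove it.

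**Arm difference** (control true 12%, s = 0.30, f = 0.4).

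- No true effect, same reply pattern in both arms: difference 0.0.
- No true effect, control 60% / 60%, intervention 80% / 50%: 17.9% − 12.0% = +5.9 points, or +3.5 points with earlier stoppers counted as no.
- No true effect, control 70% / 50%, intervention 60% / 60%: 12.0% − 16.0% = −4.0 points, or −2.5 points with the rule. The direction is therefore not fixed.
- True difference 8 points (12% against 20%), 70% / 50% in both arms: 25.9% − 16.0% = 9.9 points. A shared pattern creates no false effect but can stretch a real risk difference. The odds ratio is unchanged, because the odds among repliers are the true odds times a/b in each arm.

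**Duration.** For a woman breastfeeding at the six-month survey, a no at 12 months places stopping between 6 and 12 months (interval-censored). A yes censors her at 12 months. No reply censors her at 6 months. In none of the three cases is a number of days observed.

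**The case against.** The strongest case against has four parts.

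**Earlier reports are not discarded in the text.** A reader might infer that the plan ignores women who have already said they stopped. No section says so. The trial collects days of any breastfeeding and reasons for cessation, so a carry-forward rule could be applied, and such a rule is commonly left to the analysis plan. This stands: silence on the rule is not an error.

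**The bias is not shown.** A reader might infer that 12-month prevalence will be overstated. That needs reply to depend on feeding status, and the article gives no reply rate. It is also tempting to say that most women will have stopped by then. The 75% in the Analysis section derives from stopping exclusive breastfeeding by six weeks, and no six-month rate of any breastfeeding is given. If most have stopped, using their earlier reports confines the uncertainty to the remainder. Differential reply by arm is possible but not documented: the research team collects the data in both arms, and peer support is planned for six months. All of this stands, so the point is a risk of bias of unknown size.

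**Duration is not unmeasurable.** This also stands: the replies give interval- and right-censored data. The stated objective runs only to six months.

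**The repeat-contact rule might apply.** The 12-month text sits in the same list as the surveys, and the abstract's wording may describe a short instrument rather than rule out reminders. This is fair as far as it goes: the sections do not contradict each other. But the rule's trigger is a failed telephone call and its content is a survey link, so as written it does not reach a contact made only by text.

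What the objection does not answer is the missing stopping age and the absence of a stated reminder. Both are data-capture choices.

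**Conclusion.** The point holds as a minor, inexpensive improvement. Outcome (j) is at risk of non-response bias. On an assumed true 12% with assumed reply rates, the excess runs from 0 to about 9 points; it is 0 when reply does not depend on feeding status, and it changes with the assumed prevalence as tabulated. A false arm difference under no true effect arises only if reply patterns differ by arm, and it can go either way. For women still breastfeeding at six months, outcome (c) is interval-censored, censored at 12 months or censored at 6 months, although it is listed without a time limit. The documents do not support saying that the outcome is biased, that earlier reports are ignored, or that duration beyond six months cannot be measured. Outcome (j) is the last of ten secondary outcomes. The primary outcomes, the 80.1% power figure and the survival analysis of exclusive breastfeeding are unaffected.

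**What to change.** 1. Add one item to the 12-month text: if breastfeeding has stopped, how old was the baby when it stopped?
2. In the Data collection section, extend the existing limit of up to three sends over three weeks to the 12-month text, identically in both arms.
3. Define 12-month status as no for any woman who reported at an earlier survey that all breastfeeding had ended, and use the text for the rest.
4. If the stopping-age item is not added, state that outcome (c) is censored at six months.

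The cost is one extra text item, reminder messages and a few lines of outcome definition. The downsides are slightly more burden on respondents and misclassification of the rare woman who relactates. The item and reminders need to be in place before the 12-month contacts are made, because missed stopping ages are hard to recover reliably afterwards.
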